## Abstract

**Background:**

Evidence suggests that movement patterns, including physical activity, sedentary behavior, and sleep duration, throughout a 24-h period, have a significant impact on biological processes and health outcomes for both young and adult populations. However, 80% of adolescents worldwide are not sufficiently active, and many children do not meet international physical activity recommendations for their age. Thus, the aim of this study is to evaluate the impact of a 12-week gamified family-based health and exercise intervention on physical fitness, basic motor competencies, mental and behavioral health, and adherence to 24-h movement guidelines in children aged 4 to 5 years old. The study will evaluate changes in sedentary levels, physical fitness, basic motor competencies, mental and behavioral disorders, adherence to the exercise program, and compliance with physical activity recommendations. In addition, the aim of this protocol is to describe the scientific rationale in detail and to provide information about the study procedures.

**Methods/design:**

A total of 80 children, aged 4 to 5 years old, will be randomly assigned in a 1:1 ratio to one of two groups: the exercise group and the routine care group. The exercise group will undergo a 12-week exercise intervention, followed by a 12-week follow-up period. On the other hand, the routine care group will undergo a 12-week period of routine care, followed by a 12-week follow-up control period. The exercise program will be implemented in a family setting and facilitated through a gamified web platform with online supervision, with the hypothesis that it will have a positive impact on physical fitness, anthropometric measures, basic motor competencies, and adherence to 24-h movement guidelines.

**Discussion:**

The results of this study will provide valuable insights into the impact of a gamified, family-oriented health and exercise program on various aspects of health, including physical fitness, basic motor competencies, mental and behavioral well-being, and adherence to 24-h movement guidelines. The findings will contribute to closing the gap in current knowledge on the effectiveness of these types of interventions for children and their parents. These findings will also contribute to  the development of future guidelines for promoting physical activity in children who do not meet the World Health Organization’s recommended levels. An online “3, 2, 1 Move on Study” is believed to increase accessibility, promoting health equity, and reducing economic barriers for all children and their families across diverse social groups.

**Trial registration:**

Trial registration: NCT05741879. Registered February 14, 2023, Version 1.

## Administrative information

Note: the numbers in curly brackets in this protocol refer to SPIRIT checklist item numbers. The order of the items has been modified to group similar items (see http://www.equator-network.org/reporting-guidelines/spirit-2013-statement-defining-standard-protocol-items-for-clinical-trials/).

## Introduction

### Background and rationale {6a}

Early childhood is a crucial period for the development of physical, social, and cognitive abilities and the formation of healthy lifestyle habits that can extend into adulthood [1–3]. Unfortunately, physical inactivity is one of the leading causes of mortality worldwide, contributing to numerous health issues such as weight gain, obesity, and non-communicable diseases such as breast and colon cancer, diabetes, and heart disease [4]. There is strong evidence that the pattern of movement behaviors, including physical activity, sedentary behavior, and sleep duration, throughout a 24-h period affects biological processes and can impact health outcomes in both young and adult populations [5–7]. Regular physical activity has been shown to prevent and manage non-communicable diseases [8]. Unfortunately, 80% of adolescents globally are not sufficiently active [9], and many children do not meet international physical activity recommendations for their age [10]. In 2016, the Foundation for Nutritional Research, Physical Activity in Children and Adolescents reported that half of the population in Spain did not meet these recommendations [11]. The decline in physical activity between the ages of 11 and 15 is a concerning trend in most European countries, including Spain, with a more pronounced drop in girls (over 60%) [12]. It is important to address this issue to promote healthy physical and mental development in children.

In 2019, the World Health Organization (WHO), at the request of the Commission to End Childhood Obesity published the recommendations for physical activity, sedentary behavior, and screen and sleep time for children under the age of 5. According to these guidelines, children aged 3 to 5 years should engage in at least 180 min of physical activity of any intensity each day, including at least 60 min of moderate-to-vigorous-intensity physical activity [13]. Despite the numerous benefits of physical activity for young children, many preschoolers do not meet these recommendations [14]. A study conducted in Spanish children and adolescents aged 3 to 16 years old found a decline in physical activity levels and an increase in both screen and sleep time [15]. The authors of the study noted that preschool children aged 3 to 4 years old reduced their total PA by 92 min per day and increased their screen time by 2.2 h per day. The WHO recognizes the need for further high-quality studies that examine the full 24-h day of physical activity and a broader range of health indicators such as motor, cognitive, and psychosocial development and the long-term effects of early interventions. Additionally, studies that consider confounders such as diet and that establish standardized procedures and objective measurements to enable comparison between studies are also needed [16].

Physical activity plays a crucial role in the growth and development of preschool children, providing both immediate and long-term benefits for physical and psychological well-being [17, 18]. A recent systematic review demonstrates a positive association between physical activity and brain structure in various regions of the brain [19]. There is a significant correlation between brain structure and cognitive functions, indicating that a healthy brain structure can improve human functionality [19]. Another meta-analysis addresses the impact of physical exercise on executive functions in preadolescents children, adolescents, and young adults, concluding that short periods of high-intensity physical exercise lead to immediate improvements in executive functions. However, there is limited research on the effect of long-term exercise programs on academic and cognitive performance [20]. Additionally, the evidence for this age group is still relatively small compared to that of children and teenagers between 6 and 17. Currently, there is no evidence on the cost-effectiveness of these interventions in children under 5 years of age and their parent(s) [13].

### Objectives {7}

The objective of this study is to evaluate the impact of a 12-week gamified family-based health and exercise intervention through a gamified web platform with online supervision on physical fitness, basic motor competencies, mental and behavioral health, and adherence to 24-h movement guidelines in children aged 4 to 5 years. It is based on the global recommendations for 24-h movement [13] and focuses on promoting behavior change through family and community-level interventions without the need for additional equipment or facilities. The study will utilize a combination of anthropometric tests, objective techniques such as accelerometry, and assessments of physical fitness and motor competencies, along with questionnaires on eating habits to address confounding factors [21–23].

We propose a hypothesis that a 12-week physical exercise and lifestyle improvement program, implemented in a family setting and facilitated through a gamified web platform with online supervision, will have a positive impact on physical fitness, basic motor competencies, and adherence to 24-h movement guidelines in children aged 4 to 5 years old.

### Trial design {8}

The “3, 2, 1 Move on Study” trial will be a monocentric, single-blind parallel-group randomized controlled trial. All items from the ClinicalTrials.gov registry platform can be found within the protocol. The protocol will be developed according to the Standard Protocol Items: Recommendations for Interventional Trials (SPIRIT) guidelines for randomized controlled trial (RCTs) [24].

## Methods: participants, interventions, and outcomes

### Study design {9}

This pragmatic trial is currently taking place at “Iturrama Primary Care” (Pamplona, Navarra, Spain). This site has participated in previous clinical trials. For more details, refer to the Clinical Trials Registry: NCT05741879. The site is supported by associate investigator (AI) pediatrician leaders, who provide ongoing clinical expertise and support for the study. We will recruit eligible participants from general pediatrician wards at site.

### Eligibility criteria {10} and recruitment {15}

A total of 80 children of both sexes between the ages of 4 to 5 years old will be recruited from the “Iturrama Primary Care” (Pamplona, Navarra, Spain). Participants will be admitted if their parent(s)/guardian(s) have provided informed consent for their participation in the project and if, according to their pediatrician, they do not have physical or mental disorders that would prevent them from completing the assessment tests or participating in the exercises provided in the intervention program. It is a requirement to have at least one parent/guardian answer the questionnaires included in the protocol. Participants (children) who at the start of the project present a psychiatric disorder or chronic illness that limits their participation in physical activities, those who do not comply with the established procedures, and those who do not understand the Spanish language will be excluded from the study.

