### Intervention descriptions {11a}

Participants will be randomly assigned in a 1:1 ratio to one of two groups: the exercise group and the routine care group. The exercise group will undergo a 12-week exercise intervention, followed by a 12-week follow-up period. On the other hand, the routine care group will undergo a 12-week period of routine care, followed by a 12-week follow-up period. If participants are not engaging 2 times per week, the research team will reach out through email and/or phone to get a clear explanation as to why and to motivate the participants to continue. If the participants do not perform 70% of the training (or 17 out of 24 sessions), they will not be allowed to continue participation. The overall study procedure is illustrated in Fig. 1.

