### Participant timeline {13}

The outcome measures will be assessed at four time points [at baseline, at week 0 (T0), week 12 (T1), and week 24 (T2)], and the parent(s)/guardian(s) will be reminded to complete the questionnaires within a week. If needed, the research assistants will schedule an interview to complete the questionnaires on a tablet (Fig. 3).

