## Assignment of interventions: blinding

### Who will be blinded {17a}

The assignment password will be kept in a confidential file in the Navarrabiomed center and will be opened at the end of the study’s analyses. To ensure masking, an alpha-numerical code will be assigned to each study group. This code will be delivered to the associated researcher and will not be revealed to the investigators in charge of processing the data until the analysis of the coded interventions is completed. Additionally, the researchers from the Navarrabiomed center will be responsible for preparing reports for the participants’ safety committee to verify the progress of the study. Following the conclusion of the baseline examination, the appropriate envelope will be opened by a study researcher, and the participants will be informed about their group allocation. Assessors of outcomes will be blinded to patient data, including allocation at baseline and follow-up. Blinding will be used for all specialized analyses. Owing to the nature of the study, patients cannot be blinded to the exercise training modality.

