## Statistical methods

### Statistical methods for primary and secondary outcomes {20a}

The study will adhere to the intention-to-treat principle and use the baseline observation carried forward imputation method, where missing data will be replaced by baseline values [39]. The final analysis population will be described and any differences from the enrolled population will be reported. Participants who drop out of the study may still be included in the analysis, although their data will provide less information and lower the estimated effects variance. Adherence will be measured as the number of completed sessions divided by the total number of sessions, expressed as a percentage. The first step of the analysis will be to calculate descriptive statistics for the overall sample and between groups. Since this is an experimental design with primary and secondary outcomes measured at three timepoints - baseline (t0 = week 0), post-intervention (t1 = week 12), and after a 12-week follow-up period (t2 = week 24) - for the two study groups (exercise and routine care), a comparative analysis between the measurements will determine the differences. A linear mixed model with repeated observations will be used for these comparisons, when appropriate, for each dependent variable. Subsequently, multivariate analysis will be carried out, and the autocorrelation between repeated measures will be taken into account. We will use longitudinal analysis methods, such as a generalized estimating equation approach, to control the differences among measurements at baseline and to incorporate incomplete observations into this analysis. Pearson correlations will be calculated between the maximal values of the primary and secondary outcomes. All analyses will be 2-sided and a significance level of *α* ≤ 0.05 will be used for the primary analysis.

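### The eligibility section's compliance exclusion has no definition, threshold or time limit, so it permits removal of a randomised child and is not reconciled with intention to treat

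*Protocol article*

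**What the plan says.** One sentence in Eligibility criteria {10} and recruitment {15} holds three exclusions. It opens with "Participants (children) who at the start of the project present a psychiatric disorder or chronic illness that limits their participation in physical activities", continues with "those who do not comply with the established procedures", and ends with children who do not understand Spanish; all three groups are to be excluded. The same section adds a condition on families: "It is a requirement to have at least one parent/guardian answer the questionnaires included in the protocol".

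Four other parts of the protocol article bear on it:

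- Intervention descriptions {11a}: "If the participants do not perform 70% of the training (or 17 out of 24 sessions), they will not be allowed to continue participation". The Routine care group section carries a similar bar, again tied to training.
- Participant timeline {13}: parents are reminded to complete questionnaires within a week, and then "If needed, the research assistants will schedule an interview to complete the questionnaires on a tablet".
- Who will be blinded {17a}: "Following the conclusion of the baseline examination, the appropriate envelope will be opened by a study researcher", and families then learn their group. Section {17b} calls the design open label, with only outcome assessors blinded.
- Statistical methods {20a}: "The study will adhere to the intention-to-treat principle". Missing values are replaced by baseline values, dropouts may be included, and the final analysis population is allowed to differ from the enrolled one provided the difference is reported.

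**The concern.** Eligibility criteria should be settled before allocation. Compliance is conduct, and most of it is seen only once a child is in the study. An exclusion for non-compliance with no end date can therefore act after randomisation, when the family knows its arm and staff may know it too. With no threshold, each case is left to judgement.

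Two things are at stake. The first is selection: if exclusion depends on behaviour that differs by arm and is related to activity, the remaining groups are no longer those that were randomised. The second is avoidable loss of data: a child excluded for missing one procedure may have been able to supply the others, including accelerometry at weeks 12 and 24. A later analysis plan cannot recover measurements that were never taken.

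**Working it through.** No stated figure decides this point, so the check is mainly a comparison of texts.

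1. **Timing.** In the exclusion sentence, the reference to the start of the project grammatically governs only the psychiatric and chronic-illness clause. The compliance clause has no time point of its own.
2. **Scope.** The procedures are not named. They could mean consent, baseline tests, later accelerometer wear and testing, questionnaires, training, or all of these. No arm is specified.
3. **Is removal after entry foreign to this protocol?** No. {11a} and the Routine care group section both bar children from continuing for insufficient training. Reading the eligibility clause the same way is natural, though not compelled.
4. **Does the analysis section resolve it?** Only in part. Intention to treat with baseline carry-forward would keep an excluded child in the analysis, but inclusion of dropouts is worded as permission and the analysis population may depart from the enrolled one. Two outcomes remain open: the child is left out, which breaks intention to treat, or the child is kept with baseline values in place of outcomes that could have been observed.
5. **Does the timeline section agree with exclusion?** No. It treats a late questionnaire as something to be completed with help.

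**Bias.** If excluded children are left out of the analysis and average d min/day less moderate-to-vigorous activity than those kept, the bias in the group difference is (p1 − p0) × d, where p1 and p0 are the proportions excluded in each arm. With equal exclusion it is zero. With d = 10 and 15% against 5%, it is 0.10 × 10 = 1.0 min/day; with 25% against 5%, it is 0.20 × 10 = 2.0 min/day. The protocol gives neither d nor the proportions, so these figures only show how the formula behaves.

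**Precision, as an illustration.** Sample size {14} gives 42 per group, 10% dropout and a 5-minute difference, but no SD. After dropout, 42 × 0.9 = 37.8 children per group remain. Two-sided power is approximately Φ(5 × √(n/2)/SD − 1.96).

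- An assumed SD of 7.78 min, back-solved from about 38 per group at 80% power, gives 0.798 at n = 37.8.
- If a further 5%, 10% or 20% are excluded and left out, n is 35.9, 34.0 or 30.2 and power is 0.777, 0.755 or 0.705.
- With larger assumed SDs, going from 38 to 36 per group lowers power from 0.587 to 0.564 (SD 10) or from 0.306 to 0.293 (SD 15).
- If 10% or 20% of 42 per group are instead kept at baseline values, with no change in controls and the same SD of 7.78, the 5-minute effect shrinks to 4.5 or 4.0 min. Power is then 0.755 or 0.654, against 0.838 with no values replaced.

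**The case against.** The strongest reply is that the clause sits among screening criteria and can be read as one. Allocation is disclosed only after the baseline examination, so failure at consent or baseline procedures is visible before anyone knows the arm. Section {11b} also uses the exclusion criteria as a bar to inclusion for medical conditions and treats removal during the trial separately. This reading is available, and it means the clause is not one that can operate only after entry. It does not remove the ambiguity, because the text sets no such limit and other sections do remove children later.

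A reader might infer several stronger claims. The documents do not support them:

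- **That a single missed questionnaire or a removed accelerometer triggers exclusion.** No threshold is stated, and the timeline section points the other way for questionnaires.
- **That the clause concerns assessments and not training.** The procedures are undefined, so neither is ruled in or out.
- **That an excluded child disappears from every endpoint.** Section {20a} provides baseline carry-forward and allows dropouts to be analysed, and {20c} adds multiple imputation and nonignorable models. What is lost for certain is observed follow-up; the place in the analysis is left uncertain.
- **That the bias is 1 to 2 min/day.** The inputs are unsourced and assume complete deletion. A child who takes the accelerometer off has no activity value at that visit under any rule, so amending the clause would not remove that part of the loss.

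**Conclusion.** The point holds as an unreconciled conflict in the text. The compliance exclusion is undefined, has no threshold and no time limit. Read literally and beside the two training-related removal rules, it permits exclusion of a randomised child in either arm. This is at odds with the declared intention-to-treat analysis and with the way late questionnaires are handled. It does not show that the sponsor intends such exclusions, or how often they would occur.

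The certain consequence for a child so excluded is the loss of week-12 and week-24 outcomes that could have been measured, followed by either omission or substitution of baseline values. The direction and size of any bias cannot be derived from the documents. The power figures above rest on an assumed SD and assumed exclusion rates and indicate scale only. The point merits an amendment because the change is nearly free and protects the randomised comparison.

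**What to change.** 1. In the eligibility section, limit the criterion to the time before randomisation: children who do not complete the consent and baseline procedures are not randomised. Allocation is already disclosed after the baseline examination, so this fits the existing flow.
2. State that after randomisation a missed procedure makes only that outcome at that visit missing, and that every randomised child remains in the week-12 and week-24 assessments and is analysed in the assigned group. In {20a}, turn the permission to include dropouts into a commitment.
3. Reconcile {11a} and the Routine care group section with this, so that non-compliance does not end outcome assessment. Whether such a child goes on with the exercise sessions is a separate matter for the sponsor.

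The cost is a few sentences of amendment. A few children will be screened out at baseline, which narrows the sample slightly, and following up children who miss procedures takes somewhat more staff effort. Values that are truly missing, such as accelerometry from a child who did not wear the device, will still need the missing-data methods already planned.

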### Who will take informed consent {26a}

Throughout this protocol, the trial’s staff is responsible for weekly monitoring of various aspects, including regular reporting on informed consent. Prior to participating in the study, all parents or legal guardians will be required to sign an informed consent form. An email will be sent to them outlining the study’s objectives and procedures and encouraging them to ask any questions they may have. Additionally, it is advisable to seek the child’s perspective on the matter.

